### Patient enrolment

Every GP was asked to enrol from his or her daily patient flow a consecutive sample of 40 patients with a known diagnosis of hypertension, regardless of the cause for consultation. Further inclusion criteria were age 40–75 years, and continuity of care by this GP over at least six months. Emergency cases were excepted, and patients expected to die within 1 year were not included.

### Intervention

In order to address the complex issue of hypertension management in the light of absolute cardiovascular risk, we developed a multi-faceted intervention through a process of identifying barriers to implementation, e.g. comprehensibility of the new concept, and communication pitfalls. We compiled a written manual (17 pages) on the basis of the ESC-Guidelines [7] with the following chapters:

1. Introduction.

2. What is new about the "concept of global CVR?"

3. How to determine global CVR?

4. What is the likely individual benefit of the treatment of cardiovascular risk factors?

5. Two examples of decision-making.

6. Non-pharmacological therapy: motivation for behavioural change and psychosocial support.

7. Pharmacologic treatment with antihypertensive drugs.

8. Pharmacologic treatment with lipid-lowering drugs.

9. Literature.

This manual was sent by mail to all GPs (randomisation groups A and B). In addition, GPs in group A received a personal intervention including an outreach visit by a peer (30–45 min.), a feedback telephone call after three weeks (5–10 min.), and delivery of a block of 50 patient information sheets. Thus, we compared the effect of an elaborate intervention (A) with the conventional process of postal dissemination of a guideline-based manual (B), which is generally assumed to have no or little significant effect on physician behaviour [16].

During the outreach visit, peer and GP discussed the new concept on the basis of (a) our manual and (b) 3–4 suitable cases selected by the peer from this GP's baseline data. The cases were chosen to include at least one patient with a history of CVD, and at least two patients without such a history; of the latter one at low risk (SCORE < 5%), and one at high risk (SCORE > 5%), respectively. The discussion of the GPs' respective patient cases included feedback elements, and served as concrete examples to demonstrate the paradigmatic changes of the CVR concept to the GP. Furthermore, the GPs were instructed how to use the SCORE calculator of global cardiovascular risk (print version, included in the manual), and additional patient information sheets.

Three practising GPs ([name]) were trained to explore GPs' understanding, beliefs, and attitudes during the initial phase of the conversation in order to tailor the concept's message to the individual colleague they were talking to. The process of standardisation was facilitated by a dialogue draft for the outreach visit, regular audit-meetings, and personal feedback from a passive observer who attended the first three visits of each peer.

### Our intervention focused on five key messages

1 Therapeutic decisions in the management of hypertension should always be preceded by an estimation of absolute CVR.

2 Within certain limits, there are no fixed targets for blood pressure or cholesterol level. Rather, the attainable absolute risk reductions by lowering blood pressure or taking a statin depend on the absolute CVR before treatment.

3 All patients with manifest cardiovascular diseases (CVD) are candidates for intensive treatment because of their very high recurrence risk for CVD. In primary prevention, risk factor treatment should intensify with rising CVR, whereas patients with low CVR (defined by SCORE < 5%) have no or little proven benefit from treatment.

4 There are frequently several options to reduce cardiovascular risk. If pharmacological treatment of one risk factor remains unsatisfactory, e.g. refractory hypertension or intolerable side effects of anti-hypertensive drugs, then other options should be considered, such as prescription of a statin in this patient regardless of a "normal" cholesterol level.

5 The explanation of individual CVR is meant to enhance communication between physician and patient, represents an opportunity to invite the patient to take part in a process of shared decision making, and can be a potentially powerful vehicle to promote patient autonomy.

### Data collection

Patient enrolment and recording of baseline data took place before randomisation. Follow up data collection was conducted 6 to 9 months after the intervention. We employed a self-developed paper documentation because of the limited extent and availability of routine computerised data.

At baseline, the documentation on each patient included age, sex, smoking habits, and history of one or more of the following: diabetes mellitus, nephropathy, and manifest cardiovascular disease (namely, coronary artery disease, cerebrovascular disease, and peripheral artery disease). In addition, the GPs were requested to indicate drugs relevant for cardiovascular disease, i.e. antihypertensive, lipid-lowering, and antiplatelet drugs. The actual blood pressure reading (at enrolment) and the latest cholesterol measurement (before enrolment) were also noted.

At baseline, GP's were also asked to judge the perceived quality of the doctor-patient-relationship for each patient, and to estimate the patient's CVR (as a 10-year-mortality-risk) on a Likert scale of 1–5.

In addition, we issued a patient questionnaire at baseline to all enrolled patients asking for CVD family history, education, physical training, perceived quality of doctor-patient-relation, personal interest in taking part in treatment decisions, and two questions concerning their knowledge of global CVR.

At follow-up, actual levels of blood pressure and cholesterol were documented by practice nurses. New onset of diabetes mellitus, nephropathy, or cardiovascular events were recorded. GP's were requested to note any changes in cardiovascular medical treatment. Smoking status was updated.

### Data Retrieval and Monitoring

Every GP received instruction on study procedures individually by one of the three peers. At baseline, data sheets were directed to GPs only, but at follow-up there were different data sheets for practice nurse and GP, respectively, restricting the workload of the GPs to data only they could provide. Data sheets were personally collected by the peers at baseline, and sent by mail by the GPs at follow-up. Data were entered into electronic sheets by medical students. Practice nurses or, where necessary, GPs were contacted if inconsistencies occurred or to complete missing data.

In order to monitor the quality of the data submitted by the GPs at baseline, at the end of the study we issued a data sheet to the practice nurses requiring them to re-enter the baseline data for blood pressure and cholesterol from the electronic record. Since the written baseline data sheets had been collected from the GPs, we regarded it as unlikely that the nurses or GPs would recall after follow up what numbers had been entered at baseline. We will examine the congruence of the data documented by the GPs on the baseline forms with the data referring to the same calendar day entered by the practice nurses some 6–9 months later.

### Incentives for participation

At recruitment, each GP was offered compensation of € 300 for an estimated total workload of at least 6 hours, plus € 40 for the responsible practice nurse. In addition, practice nurses involved in the monitoring process received € 15 each.

### Outcome measures

We will calculate changes in global CVR, mean blood pressure, total cholesterol, smoking rate, blood pressure control rate, and prescription rates of CVR-lowering drugs (ASS and statins).

These outcome measures are to be calculated separately for three different subgroups of patients defined by their CVR:

Group I: Patients with a history of manifest cardiovascular disease (CVD).

Group II: Patients with high CVR (SCORE ≥ 5%), no history of CVD.

Group III: Patients with low CVR (SCORE < 5%), no history of CVD.

### Statistical analysis

The primary analysis includes all randomised patients of group II with global CVR determinations at baseline (ITT population). CVR values at baseline as well as at follow-up will be transformed on the log-odds scale (multiplicative model). In case of missing follow-up values, a LOCF (last-observation carried forward) imputation will be performed, i.e. the baseline determination will be imputed as follow-up determination. For the primary analysis, a two-level random coefficient model will be fitted to the data with patients nested in physicians modeled as random effects. This model takes the correlation structure resulting from cluster randomisation into account and allows for differences between physicians in treatment effects. The primary analysis will compare the baseline-adjusted follow-up means between random groups at a significance level of 0.05, two-sided.

As sensitivity analyses, calculations will be repeated for the complete cases population and for a dataset with missing values imputed using an EM algorithm.

Secondary analyses will be in the complete cases only. Analogous to the primary analysis, mixed models will be fitted for the secondary endpoints in group I, group II and group III separately.

In the exploratory part of the analysis, the covariates age, sex, social status, and perceived quality of the respective doctor-patient-relationship will be added as confounders and potential effect modifiers to the statistical model. By backward selection, optimal models will be identified and reported.

Calculations will be performed with SPSS and STATA, last available versions.

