### Anticipated dropouts and sample size calculation

Sample size calculation refers to research question 1 (see above). In order to demonstrate an effect of reducing mean calculated CVR by a tenth in the subgroup of patients with high CVR (SCORE ≥ 5%, no history of cardiovascular disease) with a power of 80%, we calculated a necessary initial sample size of 2 × 51 recruited GPs enrolling 40 patients each. We estimated a GP drop out during the enrolment phase of 5%, a patient enrolment rate of 95%, a GP drop out between baseline and follow up of a further 5%, and a patient drop out between baseline and follow up of 10% (resulting in 3146 patients enrolled by 92 GPs). The sample size calculation was based on the assumption of a standard deviation of 0.44 for the CVR changes on the log-odds scale, an intra-class correlation of 0.2 and a proportion of 40% high risk patients in the total sample, the latter derived from a pilot study with 330 patients cared for by 20 GPs. According to these assumptions, 2 × 816 patients were required for the primary analysis in the high risk group.

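### Carrying baseline CVR forward in the primary analysis shrinks the estimated effect by the share of patients lost, and can create a false arm difference if loss is unequal and CVR changes in both arms

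*Protocol article*

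**What the plan says.** The Statistical analysis section of the protocol article defines the primary population as every randomised group II patient (SCORE at or above 5%, no history of CVD) with a baseline CVR. Where follow-up CVR is missing, "a LOCF (last-observation carried forward) imputation will be performed, i.e. the baseline determination will be imputed as follow-up determination". A two-level mixed model then compares baseline-adjusted follow-up means between arms "at a significance level of 0.05, two-sided".

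Two sensitivity analyses are named. One repeats the calculation in complete cases. The other repeats it "for a dataset with missing values imputed using an EM algorithm". Secondary analyses use complete cases only.

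The Data collection section describes a single follow-up round, 6 to 9 months after the intervention. The section on anticipated dropouts and sample size expects 5% of GPs to be lost between baseline and follow-up, and "a patient drop out between baseline and follow up of 10" per cent. It aims to detect an effect of "reducing mean calculated CVR by a tenth".

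**The concern.** With one follow-up, the last observation is always the baseline value, so carrying it forward fixes the change at zero for each lost patient and for every patient of a GP who leaves. This raises three issues.

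- **Dilution.** Zero changes are averaged into both arms, so the estimated arm difference shrinks towards zero. The Design section justifies comparing the costlier intervention with a cheap one by the benefit it adds, so the size of the estimate matters as well as its p-value.
- **Bias under unequal loss.** If CVR changes in both arms, imputed patients miss that change, and the arm that loses more patients appears to have changed less. A common change is plausible: group II is selected on a baseline threshold, using a blood pressure reading taken at enrolment, so regression to the mean is expected, and both arms receive the manual. Unequal loss is plausible too: the trial is not blinded, only one arm gets a visit and a feedback call, and follow-up sheets are posted back by the GPs.
- **The supporting analysis.** A single EM-completed dataset treats imputed values as if they had been observed.

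In addition, the primary CVR result in group II and the secondary results on its components (blood pressure, cholesterol, smoking) would follow different missing-data rules and rest on different patients.

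**Working it through.** **Inputs from the document.** Test "at a significance level of 0.05, two-sided"; "a standard deviation of 0.44 for the CVR changes on the log-odds scale"; "an intra-class correlation of 0.2"; 2 × 51 GPs with 40 patients each; 40% high risk; losses of 5% of GPs and 5% of patients at enrolment, then 5% of GPs and 10% of patients before follow-up.

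**Step 1: reproduce the plan's attrition.** GPs: 102 × 0.95 × 0.95 = 92.05, so 92. Patients: 92 × 40 × 0.95 × 0.90 = 3146.4. Both agree with the stated 92 and 3146, so the dropout figures are being read as the plan meant them. The 3146 excludes patients lost before follow-up, whereas the primary analysis keeps such patients in group II, with zero change.

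**Step 2: share imputed.** 1 − 0.95 × 0.90 = 0.145.

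**Step 3: dilution.** If loss is unrelated to response, LOCF estimate = (1 − 0.145) × true effect = 0.855 × true effect. The mean baseline CVR is not given, so the log-odds equivalent of a 10% reduction is a range:

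| Basis for a 10% reduction | True log-odds effect | Under LOCF |
|---|---|---|
| ln 0.9 | 0.105 | 0.090 |
| assumed mean CVR 10%: logit(0.10) − logit(0.09) | 0.116 | 0.0995 |
| assumed mean CVR 15% | 0.123 | 0.105 |

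In percentage terms, 1 − exp(−0.0901) = 8.6%.

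**Step 4: simulation of the planned model.** 3000 runs per scenario; 48 GPs per arm with 15 high-risk patients each; SD 0.44; ICC 0.2; baseline-adjusted random-intercept REML model; dropout independent of outcome given arm. The baseline log-odds SD of 0.6 is an assumption. True effect 0.116, equal loss of 14.5%:

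| Analysis | Estimate | Model SE | Empirical SE | Power |
|---|---|---|---|---|
| Observed follow-up only | 0.115 | 0.047 | 0.047 | 69.3% |
| LOCF | 0.099 | 0.040 | 0.040 | 69.1% |

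**Step 5: no true effect.** Expected false difference = common change × difference in missing share. Assumed unequal loss: group B 1 − 0.90 × 0.85 = 23.5%, group A 1 − 0.98 × 0.95 = 6.9%, a difference of 0.166. A common fall of 0.1 gives 0.0166 and a fall of 0.2 gives 0.0332. Simulated (a negative value favours the complex intervention):

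| Common fall | Loss B / A | LOCF estimate | LOCF type I error | Observed-only type I error |
|---|---|---|---|---|
| 0.1 | 14.5% / 14.5% | −0.002 | 5.0% | 5.2% |
| 0 | 23.5% / 6.9% | 0.000 | 5.2% | 5.4% |
| 0.1 | 23.5% / 6.9% | −0.017 | 7.1% | 5.3% |
| 0.2 | 23.5% / 6.9% | −0.033 | 13.5% | 5.3% |

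Both conditions, unequal loss and a common change, are needed.

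**Step 6: single EM dataset.** Missing values were filled with regression predictions, without a GP term. With arm in the imputation model and a true effect, the model SE is 0.0401 against a true 0.0469; with no effect it is 0.0401 against 0.0465. The SE is therefore about 14% too small, and type I error is 9.4% to 10.0%. With arm left out, the SE is right (0.040 against 0.040) and type I error is 5.0% to 5.1%, but a true effect of 0.116 is estimated as 0.099, as under LOCF.

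**The case against.** The strongest defence is that the plan already contains the better analysis. With one follow-up, the baseline-adjusted mixed model on complete cases uses all observed follow-up values and is unbiased when missingness depends only on arm and baseline. This stands, so the point is about which analysis carries the confirmatory test. It does not remove the problem, because the 0.05 test is attached to the LOCF result.

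A second defence is that LOCF keeps every randomised group II patient and, with equal loss, errs towards no effect. Missing at random cannot be tested either: if GPs who leave never changed their practice, zero change may be nearer the truth. That is a good reason to keep LOCF as a sensitivity analysis. It does not make LOCF reliably conservative, as Step 5 shows.

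A reader might also infer more than the document supports:

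- **That LOCF costs power.** It does not to any extent that matters (69.1% against 69.3%). The shortfall from 80% in the simulation is a matter for the sample size section.
- **That unequal dropout alone produces a false difference.** Without a common change the bias is zero. The document quantifies neither the common change nor any imbalance in loss, so the type I figures illustrate assumed conditions and do not predict what will happen.
- **That the EM standard errors are bound to be too small.** This depends on whether arm is in the imputation model. The article does not give that model, and such detail may properly sit in an analysis plan that is not shown.

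**Conclusion.** The point holds in a limited form. At the plan's own dropout, the primary estimate is multiplied by 0.855 if loss is unrelated to response: 0.116 becomes about 0.099 on the log-odds scale, and a 10% reduction reads as about 8.6%. This part rests on the document's figures, except for the mean baseline CVR behind the 0.116.

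A false arm difference is a conditional risk. It needs both unequal loss and a CVR change common to both arms. Under the assumed 23.5% versus 6.9% missing and a common change of 0.1 to 0.2, type I error is 7.1% to 13.5%, against about 5% on observed values.

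The EM dataset is weak support under either imputation model examined: its SE is too small with arm included, and its effect is diluted with arm left out. The complete-case analysis is sound under its stated condition but is not the primary test. The change should be made; it is not a fatal flaw.

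**What to change.** In the Statistical analysis section:

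1. Make the baseline-adjusted mixed model fitted to all observed follow-up CVR values the primary analysis. Multiple imputation carried out by arm, respecting the GP clusters, is an acceptable alternative.
2. Move baseline-carried-forward to a sensitivity analysis.
3. Replace the single EM-imputed dataset by multiple imputation that includes arm and the GP level, so that the standard errors reflect the uncertainty of the imputed values.

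The change should be fixed before follow-up data are compared by arm.

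The cost is about two sentences and some programming for the multiple imputation. The preferred analysis is already planned and needs only to be made primary, with practically no change in power. The downside is that the primary estimate then rests on missing at random, which the retained sensitivity analyses probe.

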### Design

Prospective non-blinded longitudinal cluster-randomised intervention study. One GP (or one group practice with 1–3 GPs, respectively) represents a cluster, whereas the patients are the observation units.

After enrolling the patients, GPs were cluster-randomised into two groups, A and B. GPs of group A received a written manual by mail explaining the concept of global CVR. In addition, the GPs of this group received a tailored intervention including a clinical outreach visit (for details cf. *Intervention*). GP's of group B received only the written manual by mail with no further educative intervention.

Thus, the complex intervention (group A) is not compared to usual care, but to a low-level intervention (group B). This reflects our hypothesis that the benefit of the complex and therefore more-costly intervention may be relevant only if the effect can be demonstrated against a less-complex, low-cost intervention.

Figure 1 is a flow chart of this two-group intervention trial.

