### Participants and randomisation

We recruited GPs in the district of North-Rhine, choosing three circumscribed regions close to the cities of Düsseldorf, Cologne, and Aachen, one region for each of the three attending peers (convenience sample).

A random sample of the registered GPs in a given postal code were invited to participate by fax, and called 3–5 days later by one of the three trained peers. Incentives to participate were 1. the offer of a free and pharma-independent manual and, depending on randomisation, possibly peer training in a relevant field of General Practice; 2. the opportunity to take part in an innovative research project developed by GPs for GPs; and 3. an honorarium of € 300 for completing both data surveys (requiring a net time investment of 5 to 6 hours).

After patient enrolment and baseline data collection, the GPs (clusters) were randomised to intervention groups A and B.

In order to avoid the possibility that GPs already familiar with the concept of global CVR were accidentally over-represented in either group, we asked the GPs to estimate the individual CVR of each patient they enrolled. We compared this estimate with the respective patients' calculated CVR, and divided the GPs into two groups, according to whether their estimate is close to or far from the calculated CVR. We assumed this division to approximate a measure for *familiarity with the concept of global CVR*, and for randomisation, GPs were stratified by this attribute.

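### The randomised cluster may be a group practice of up to three GPs, but the primary model groups patients by physician; read literally, the 5% test can be too liberal

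*Protocol article*

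**What the plan says.** All places are in the protocol article, under Methods/Design.

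- **Design** defines the randomised unit: "One GP (or one group practice with 1–3 GPs, respectively) represents a cluster, whereas the patients are the observation units". Two or three GPs may therefore be allocated together.
- **Participants and randomisation** treats the two terms as the same thing: "the GPs (clusters) were randomised to intervention groups A and B".
- **Patient enrolment** works per doctor: "Every GP was asked to enrol from his or her daily patient flow a consecutive sample of 40 patients".
- **Anticipated dropouts and sample size calculation** also counts doctors: "we calculated a necessary initial sample size of 2 × 51 recruited GPs enrolling 40 patients each".
- **Statistical analysis** fits "a two-level random coefficient model will be fitted to the data with patients nested in physicians modeled as random effects" and adds: "This model takes the correlation structure resulting from cluster randomisation into account". It then says that the model allows treatment effects to differ between physicians. The secondary endpoints get mixed models of the same kind.

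The article does not say how many clusters are group practices, or whether more than one GP in any practice enrolled patients.

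**The concern.** Two levels, patient and physician, are enough only if physician and randomised cluster are the same unit. The Design section says they need not be.

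GPs randomised as one practice always share an arm, so any correlation between their patients adds to the variance of the comparison between arms. A random effect on the individual GP sets that correlation to zero. If it is in fact positive, the standard error of the primary effect is too small, the confidence interval too narrow, and the true type I error above the nominal 5%. The secondary models would inherit the same problem.

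This is not a detail left for a fuller plan. The article names the grouping factor and the number of levels, and says that they suffice.

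**Working it through.** **Inputs from the sample size section.** ICC 0.2; 40 patients per GP; patient enrolment rate 95%; patient dropout 10%; 40% high risk; 2 × 51 GPs, with 5% GP dropout during enrolment and a further 5% before follow-up.

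**The plan's own counts.**
- GPs: 102 × 0.95 × 0.95 = 92.06, given as 92.
- Patients: 92 × 40 × 0.95 × 0.90 = 3146.4, given as 3146.
- High-risk patients per arm: 51 × 40 × 0.40 = 816, the stated figure.

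All three count by GP. The number of randomised units enters none of them.

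**Assumed, because the article does not give them.**
- s: the share of GPs who work in practices with k enrolling GPs.
- r: the practice ICC, that is, the correlation between patients of different GPs in one practice. The range is 0.05 to 0.2. At r = 0.2 the whole ICC sits at practice level and GPs within a practice do not differ at all, so this is an upper bound.

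**Step 1. Patients per GP.** m = 40 × 0.95 × 0.90 × 0.40 = 13.68 high-risk patients.

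**Step 2. Variance of one GP's mean**, in units of the total variance: V = 0.2 + 0.8/13.68 = 0.2585.

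**Step 3. Variance ratio.** A GP has on average s(k − 1) colleagues in the same randomised practice, and each adds a covariance r. The true variance of the arm contrast divided by the variance under a GP-only model is

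f = 1 + s(k − 1)r/V.

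**Step 4. True type I error** = 2 × [1 − Φ(1.96/√f)].

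| Setting | r | f | Type I error |
|---|---|---|---|
| All clusters one GP | any | 1.00 | 5.0% |
| 10% of GPs in pairs | 0.05 | 1.02 | 5.2% |
| | 0.1 | 1.04 | 5.4% |
| | 0.2 | 1.08 | 5.9% |
| 30% in pairs | 0.05 | 1.06 | 5.7% |
| | 0.1 | 1.12 | 6.4% |
| | 0.2 | 1.23 | 7.7% |
| 30% in trios | 0.05 | 1.12 | 6.4% |
| | 0.1 | 1.23 | 7.7% |
| | 0.2 | 1.46 | 10.5% |

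**Step 5. Standard error, 30% in trios.** For r = 0.1 and 0.2, √f = 1.11 and 1.21. The true standard error is 11% and 21% larger than the model's. Put the other way, the model's is 1 − 1/1.11 = 10% and 1 − 1/1.21 = 17% too small.

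**Check by simulation** (t-tests on GP means, about 46 GPs per arm).
- About 20% of GPs in pairs, r = 0.05 and 0.1: 5.7% and 5.8%, against 5.4% and 5.9% by formula.
- About half in pairs, r = 0.1 and 0.2: 7.2% and 9.6%, against 7.3% and 9.6%.
- A separate simulation of the 30% trio setting, r = 0.1 and 0.2: 7.3% and 9.3%, against 7.7% and 10.5%. It kept whole practices within arms, so its share of GPs in trios was slightly below 30%.

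**The case against.** The strongest reply is that the article uses GP as its everyday word for the cluster. The randomisation section equates the two, the sample size and the stratification run by GP, and the analysis section itself speaks of the correlation due to cluster randomisation. On that reading *physicians* is shorthand for the randomised unit, the model is correct, and only the label is loose. The range of 1 to 3 GPs for a group practice also includes one, so every cluster may have had a single enrolling doctor.

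Much of this stands. A reader might infer that the primary test is too liberal. The documents do not support that, because it needs three things they do not establish: that *physicians* means individual doctors, that some practices had two or more enrolling GPs, and that patients of different GPs in a practice are positively correlated. A reader might also infer clusters of 3 × 40 = 120 patients; the article never describes one. Nor does "At follow-up, actual levels of blood pressure and cholesterol were documented by practice nurses" prove practice-level correlation. It makes some plausible, but the article does not say that nurses were shared between GPs.

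What the reply does not remove is the mismatch. Design provides for clusters with several GPs, while the analysis section names the physician, and its remark on treatment effects differing between physicians reads naturally as individual doctors. An analyst following the text could well group by GP.

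**Conclusion.** The point holds as a conditional one. The Design, Participants and randomisation, and Statistical analysis sections do not agree on the unit. Followed literally, the primary model ignores any correlation between patients of different GPs in one randomised practice.

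The consequence runs from nil upward. If every cluster is one GP, the test keeps its 5%. With few GPs in pairs the inflation is small; with 30% in trios it is material, though the 10.5% at the top of that range rests on the bounding practice ICC of 0.2. The shares and practice ICCs are all assumptions, combined with the plan's ICC of 0.2 and 13.68 high-risk patients per GP, so no single corrected error rate can be given.

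**What to change.** - **Statistical analysis:** state that the random effect sits on the randomised unit, meaning the single-handed GP or the group practice. Where a practice has several enrolling GPs, nest GP within practice as a middle level, or use cluster-robust standard errors at practice level.
- **Secondary models:** use the same grouping.
- **Sample size section:** give the number of randomised clusters beside the number of GPs, and say how many clusters have more than one enrolling GP.

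The cost is a sentence or two of text and a practice identifier in the dataset, which randomising by practice already requires. The downside is a slightly wider interval if practices with several GPs took part. If every cluster is one GP, the results do not change.

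### GPs are randomised within familiarity strata, but the primary model names no stratum term; if the stratum is prognostic, the reported standard error is too large and the test conservative

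*Protocol article*

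**What the plan says.** Participants and randomisation (protocol article): each GP estimated the risk of every enrolled patient. GPs were then split into two groups by how well those estimates agreed with the calculated risk. The split is taken as a proxy for familiarity with the CVR concept, and "for randomisation, GPs were stratified by this attribute". The stated reason is balance: "In order to avoid the possibility that GPs already familiar with the concept of global CVR were accidentally over-represented in either group".

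Statistical analysis (protocol article): for the primary analysis "a two-level random coefficient model will be fitted to the data with patients nested in physicians modeled as random effects". The comparison is then fixed: "The primary analysis will compare the baseline-adjusted follow-up means between random groups at a significance level of 0.05, two-sided". Baseline CVR is the only covariate named. Secondary endpoints get mixed models built in the same way. In the exploratory part, "the covariates age, sex, social status, and perceived quality of the respective doctor-patient-relationship will be added as confounders". The familiarity stratum appears in none of these places, nor in the two sensitivity analyses.

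**The concern.** When allocation is balanced within strata, differences between strata largely cancel out of the difference between arms. The true sampling variance of the treatment effect is therefore smaller than under simple randomisation, to the extent that the stratum predicts the outcome. A model without the stratum does not register this. It leaves the stratum's contribution in the between-GP variance component and reports a standard error that includes it.

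The result is a confidence interval wider than it need be and a test whose real size lies below the nominal 0.05. Neither produces a false positive, but both make a real effect harder to show. In this trial a GP-level factor acts on the component that dominates precision, because the intra-class correlation is assumed to be 0.2 and each GP contributes only about 14 high-risk patients.

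**Working it through.** **Inputs from the section on anticipated dropouts and sample size calculation.** SD of CVR change on the log-odds scale 0.44; intra-class correlation 0.2; 40% of patients at high risk; 40 patients per GP; 95% patient enrolment; 10% patient dropout; 92 GPs remaining.

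**The plan's own counts.** 92 × 40 × 0.95 × 0.90 = 3146, as stated. 51 × 40 × 0.40 = 816, the stated number per arm. The plan gives no standard error or interval width to reproduce.

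**Units used here.** 92 / 2 = 46 GPs per arm. High-risk patients per GP: m = 40 × 0.95 × 0.90 × 0.40 = 13.68.

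**Assumptions.** R² is the share of between-GP variance that the stratum explains after baseline adjustment. The document does not give it, so 0 to 20% is shown. Arms are taken as balanced within strata, and the SD of change stands in for the residual SD of the baseline-adjusted outcome.

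**Formula.** Variance of the arm difference in GP means = 2 × 0.44² × [0.2 × (1 − R²) + 0.8/m] / 46.

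- *Reported by a model without the stratum:* 0.8/13.68 = 0.0585, so the bracket is 0.2585. The variance is 2 × 0.1936 × 0.2585 / 46 = 0.002176, so SE = 0.0466.
- *True at R² = 0.20:* the bracket is 0.16 + 0.0585 = 0.2185, so SE = 0.0429.
- *Ratio:* √(0.2585/0.2185) = 1.088. The actual alpha is the two-sided normal tail beyond 1.96 × 1.088 = 2.13, which is 0.033.

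| Assumed R² | Interval width, stratum omitted / included | Actual alpha, stratum omitted |
|---|---|---|
| 0 | 1.00 | 0.050 |
| 0.05 | 1.02 | 0.046 |
| 0.10 | 1.04 | 0.041 |
| 0.20 | 1.09 | 0.033 |

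**Sensitivity to the analysis set.** The number of GPs cancels from the ratio, so only m matters. The primary analysis carries baseline values forward for missing follow-up, so m is nearer 40 × 0.95 × 0.40 = 15.2. At R² = 0.20 that gives √(0.2526/0.2126) = 1.09, the same to two decimals.

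**Simulation check.** 20,000 simulated trials of GP means, with balanced strata, 46 GPs per arm and m = 14:

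- *R² = 0.10, stratum omitted:* mean reported SE 0.0464 against an empirical SD of 0.0444; type I error 4.1%; coverage 95.9%.
- *R² = 0.10, stratum included:* mean SE 0.0446; coverage 95.0%.
- *R² = 0, either model:* coverage 95.2%, so nothing is gained or lost.

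**The case against.** The strongest reply is that a journal article condenses. An analysis plan that is not shown may list the stratum as a fixed effect, and the article nowhere says that baseline CVR is the only covariate. The exploratory covariates answer the third research question and were never a list of design factors. This is fair, and it limits the point to the model as published. It does not dispose of it. The section fixes the outcome scale, random structure, imputation, comparison and alpha, and names its covariates. Within that description, the one variable that constrained allocation has no place.

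A second reply is that the stated aim of stratifying was balance, and balance is achieved whatever model is fitted. That is correct. A reader might infer that the plan sought precision by stratifying and then threw it away, but the document gives no such motive. The estimator keeps the benefit of balance; only the reported standard error may fail to reflect it.

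Third, the loss may be nil. The stratum is a coarse two-way split of estimates given on a five-point scale, and its link to outcome after baseline adjustment is unknown. This stands, and is why the range starts at zero.

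Two stronger readings are tempting and are not supported:

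- *A larger effect.* Applying the 20% share to the whole variance of a GP mean gives 1/√(1 − 0.20) = 1.118, an interval 12% too wide. But the stratum can act only on the between-GP part, which is 0.2/0.2585, or about 77% of that variance.
- *Region or peer must be added too.* Recruitment used "one region for each of the three attending peers", so region is known for every GP. But the article names familiarity alone as the stratifying factor. The argument about a miscalibrated standard error therefore does not extend to region. Adjusting for it is optional and not part of this point.

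**Conclusion.** The point holds in a limited, conditional form. As published, the primary model omits the factor by which GPs were stratified. The omission causes no bias and no excess of false positives. If the stratum explains 0 to 20% of between-GP variance after baseline adjustment, the interval is 0 to 9% too wide and the actual alpha runs from 0.050 down to 0.033.

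That share is an assumption, so a loss of precision cannot be stated as certain. The figures also rest on the plan's intra-class correlation of 0.2 and on balance within strata, and they apply to the primary outcome only. The point is minor to moderate, and worth acting on because the remedy is almost free.

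**What to change.** State in the Statistical analysis section that the two-level familiarity stratum used at randomisation enters the primary model as a fixed GP-level effect, alongside baseline CVR. Carry the same term into the secondary models built on the primary one. If an analysis plan already includes it, a sentence saying so is enough. The wording should be settled before outcomes are compared by group.

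The cost is one sentence and one degree of freedom (92 GPs less two arms leaves about 90). No new data are needed, since the stratum was assigned to every GP before randomisation.
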